## Abstract

**Background:**

Juvenile idiopathic arthritis (JIA) is a common chronic rheumatic disease with no known cures, affecting children with the age of onset under 16 years. Patient-reported outcome (PRO) measures are an important basis for evaluating the impact of JIA and associated therapies, however, which is particular challenge in the pediatric setting. At present, no randomized controlled studies have investigated the effect and usability of ePROs symptom management for children with JIA.

**Methods:**

This longitudinal, randomized, controlled trial will be carried out at outpatient and pediatric wards of the Shanghai Children's Medical Center affiliated to Shanghai Jiao Tong University School of Medicine. A total of one hundred children with JIA diagnosed according to the International League of Associations for Rheumatology (ILAR) patients are randomized to receive individualized symptom management based on ePROs or routine management. The primary outcome is the mean C-Ped-PROMIS T-scores of patients in the ePROs-based group and the control group. The secondary outcomes are the trajectories of C-Ped-PROMIS T-scores and HRQOL scores, and changing relationship between them. Data were collected at 5 time points: at enrollment (“baseline”) and at the time of follow-up visits scheduled at 1, 3, 6, and 12 months.

**Discussion:**

The findings are expected to conclude that the symptom management based on ePROs for children with JIA can improve the symptom of JIA, and it is a feasible and effective way to monitor and intervene children with JIA.

**Clinical Trial:**

http://www.chictr.org.cn/showproj.aspx?proj=132769; (ChiCTR2100050503)

## Introduction

Juvenile idiopathic arthritis (JIA), defined as arthritis of unknown cause with an onset before the age of 16 and persisting for at least 6 weeks (1), is the most common rheumatic condition in childhood (2). JIA is characterized by chronic synovial inflammation of joints (1), and its pathogenesis has not been fully elucidated. The annual incidence rate of juvenile arthritis (JA), including JIA, juvenile rheumatoid arthritis (JRA), and juvenile chronic arthritis (JCA), is 0.83–25 per 100 000, and the prevalence in China is reported to be 3.8 per 100 000. JIA involves multiple organs and in combination with pain, fatigue, and depression (3), most children with JIA need long-term pharmacological treatment and regular periodic clinical follow-ups (4), and some serious cases even need to require multiple hospitalizations. The primary symptoms of JIA are joint pain, stiffness, and lameness (5), which are associated with daily activities limitation, long-term disability, and reduced health-related quality of life (HRQOL) (6). These effects can persist into adult life, profoundly affecting generic health status and HRQOL (7).

Compared with healthy peers, the HRQOL of children with JIA is hindered seriously (8), and some of them are even much lower than those of other patients with chronic diseases. JIA can also impair the quality of life of their parents and families (9), with them reporting significant labor-time loss and healthcare costs (10).

Consequently, there is a growing consensus among researchers and clinicians that ameliorating patient symptoms and improving HRQOL are the primary goals of the management of JIA (9, 11). The constant monitoring of the JIA course (such as disease manifestations, therapies effects, morbidities, functional status, and quality of life) is a key way to achieve the goals. In the past few years, many feasible instruments specific to JIA have been developed for outcome measurement. For example, the core sets of disease activity measures are used to assess whether children with JIA show clinically improvement after anti-rheumatic drug treatment (12). Recently, Juvenile Arthritis Disease Activity Score (JADAS) (13), containing four measures, was developed to assess disease activity and disease damage. In addition, the patient/parent-acceptable symptom state was estimated by patient/parent acceptable symptomatic state (PASS) (14). However, these measures are not widely used in most pediatric centers. Many authorities now have focused on patient-reported outcomes (PROs), which provide an important way to evaluate the impact of JIA course and make more individualized symptom management and treatment, which is also an effective way to achieve patient-centered care.

The key feature of PROs (15) is patients provide health information directly. Common PROs include HRQL, health status, patient satisfaction and treatment experience, psychological distress, pain, and self-efficacy (16), and PROs have been widely applicated, particularly in the oncology domain (17). To deepen and promote the PROs idea, the United States National Institutes of Health (NIH), as the main sponsor, has been developing Patient Reported Outcomes Measurement Information System (PROMIS) since 2004 (18). Pediatric PROMIS (19), a pediatric self-report item banks, was created by University North Carolina (UNC), which has been validated to be sensitive to evaluate the PROs in children with chronic pain (20), children with cerebral palsy (21), children with Crohn's disease (22), and children with JIA (23). Pediatric PROMIS can also be used as clinical trial endpoints (24).

The research team of Chinese professor [name] from Second Military Medical University has translated it into Chinese version of the Pediatric PROMIS (C-Ped-PROMIS) (25). The C-Ped-PROMIS contains eight short forms: depressive symptoms, anger, anxiety, fatigue, pain interference, peer relationships, mobility, and upper extremity function, which has been found to have good reliability and validity (25), and is suitable as a standardized tool for evaluating the PROs of children in our country. For 5- to 7-year-old pediatric child, they are too young to complete the PROs equipment. Thus, the PROMIS Parent Proxy Report Scales for Children is used to solve this problem, which has been studied as suitable for parents of children with the ages 5–7 (26). The PROMIS Parent Proxy Report Scales also have been authorized to translate to the Chinese version (25). For easy description, we refer to both Pediatric PROMIS and PROMIS Parent Proxy Report Scales collectively as C-Ped-PROMIS.

The PROs are originally paper-based through written questionnaires and/or in-person interviews (27), called “paper-based PROs.” With growing information technology, PROs are collected by devices or software, called “ePROs” (28), which were found to be more flexible, convenient, and efficient (29). Compared with paper-based PROs, the ePROs not only can avoid data entry errors and reduce missing information (30) but also can increase the overall survival among patients with cancer (31). The research team of professor [name] has developed smartphone applications (apps) with “C-Ped-PROMIS” module to collect pediatric PROs (19). This app includes three modules: “Questionnaire,” “Mine,” and “Manor,” and it can implement multiple functionalities including collecting basic information about children and their parents, visualization of PROs, and a virtual animal adoption incentive system. The main function of the “Questionnaire” module is to collect basic information and the symptom assessment questionnaires, which includes three parts: basic information, parents' entrance, and children's entrance. Parents fill in basic information about themselves and their children, as well as childhood disease information. In the parents' entrance, the parents of children aged 5–7 complete the PROMIS Parent Proxy Report Scales. In the children's entrance, children aged eight, and older independently complete Pediatric PROMIS. Moreover, taking into account the specificity of children, the ePROs use the cartoon interface and equip with voice assistants, which can announce the content of each item. For the incentive system, it was designed that at the beginning of filling in the symptom questionnaire, there will be six virtual animals on the interface, and children can choose one of them. The virtual animals will grow as the children fill out the questionnaire carefully. In the “Manor,” children can see the growth status of the virtual animals. After completing the questionnaire for the last time, we will exchange an identical animal toy for children. Based on the app, we design a new ePROs app to evaluate, monitor, and manage the PROs of children with JIA. After authorization, we add the Pediatric Quality of Life Inventory^TM^3.0-Rheumatology Module (PedsQL^TM^3.0-RM) (32) to the “Questionnaire” module for assessing the HRQOL of patients. In addition, we incorporate in the app a “Symptom Intervention” module for performing targeted and individualized interventions of children with JIA dynamically. The ePROs allow children with JIA to self-report their individualized symptoms, and the arising real-time data are available to health professionals to provide symptom management.

In summary, the JIA diagnosis and treatment are a long-term, dynamic, and complex process. The timely and dynamic symptom intervention for children with JIA is necessary for the symptom experience, and treatment needs and therapeutic effects are varied. The present human randomized, controlled, longitudinal trial is designed to evaluate the effect of symptom management for children with JIA based on ePROs.

## Hypotheses And Objectives

### Hypotheses

The symptom management based on ePROs for children with JIA will improve the HRQOL of JIA, monitor, and intervene in the symptom of children with JIA feasibly and effectively.

### Objectives

The primary objective was to assess the effect of symptom management for patients with JIA based on ePROs by comparing the C-Ped-PROMIS T-scores of patients between the ePROs-based group and the control group.

The secondary objective of this trial was to assess what extent can symptom management based on ePROs improve the HRQOL of patients by evaluating the relationships between changes in C-Ped-PROMIS and changes in the HRQOL of patients.

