#### Secondary Outcomes

The second outcomes of our study are the trajectories of C-Ped-PROMIS and HRQOL. We assessed the longitudinal changing trend of the mean T-scores of the C-Ped-PROMIS and the mean score of the PedsQL^TM^3.0-RM from baseline to 12 months after discharge. Furthermore, we examined the relationships between changes in C-Ped-PROMIS and changes in the HRQOL by evaluating the T-scores changes and PedsQL^TM^3.0-RM score changes among patients in the ePROs-based group and those in the control group.

The PedsQL^TM^3.0-RM (33) is a mature and specific tool for measuring the HRQOL of children with rheumatic diseases. It includes an age scale with five dimensions: pain (four items), daily activities (five items), treatment (seven items), worry (three items), and communication (three items), 22 items in total. There are five response options: “never,” “almost never,” “sometimes,” “almost always,” “always,” to which the scores 100, 75, 50, 25, and 0 are given, respectively. The scores of each dimension and total scale are the total score of each item divided by the number of response items, the score ranges from 0 to100, with higher scores indicating better HRQOL. The Chinese version of PedsQL^TM^3.0-RM has been verified to be a good instrument with acceptable reliability and validity and is suitable for assessing the quality of life among Chinese children with RA (37).

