### Statistical Analyses

SPSS 20.0 will be used for statistical analysis. Intention-to-treat analyses will be conducted by including all available data in the analysis. Missing data will be imputed by the multiple imputation method. A two-sided *p* < 0.05 is considered to be statistically significant. Data are first subjected to the normality tests, continuous variables that conformed to the normal distribution will be presented as the mean (SD), and do not conform to a normal distribution will be expressed as median (IQR). Categorical variables will be presented as frequencies or proportions. Comparisons between groups will be conducted using the Wilcoxon and Fisher's exact tests. Trajectories of PROs will be compared in two groups by repeated measures ANCOVA, as implemented under the general linear model. The MPLUS will be used to sort and analyze the data, and the LTA model was used to evaluate the intervention effect. In addition, subgroup analysis was carried out according to subgroups of JIA.

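### The secondary objective asks how far the intervention improves HRQOL, but names an association between two change scores, which is not a treatment effect, as the means of answering

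*Protocol article*

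**What the plan says.** All references are to the protocol article.

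- **Hypotheses.** The hypothesis opens with HRQOL: "The symptom management based on ePROs for children with JIA will improve the HRQOL of JIA".
- **Objectives.** The primary objective is framed as a comparison of C-Ped-PROMIS T-scores between the two arms. The secondary objective is framed differently: it asks how far symptom management improves HRQOL, to be answered "by evaluating the relationships between changes in C-Ped-PROMIS and changes in the HRQOL of patients". No arm comparison appears in that sentence.
- **Secondary Outcomes.** The trajectories come first: "The second outcomes of our study are the trajectories of C-Ped-PROMIS and HRQOL". HRQOL is the mean PedsQL 3.0-RM score, followed from baseline to 12 months after discharge. The association is then added: "Furthermore, we examined the relationships between changes in C-Ped-PROMIS and changes in the HRQOL", evaluated among patients of both arms.
- **Statistical Analyses.** "Trajectories of PROs will be compared in two groups by repeated measures ANCOVA". PedsQL is not named in this section.

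**The concern.** The question is causal: what does assignment to symptom management do to HRQOL? The method attached to it is a relationship between two changes that both occur after randomization. Such a relationship shows whether children whose symptom scores move also move on the quality-of-life score. It does not show whether either movement was caused by the assigned arm.

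Some association is to be expected without any intervention effect. C-Ped-PROMIS covers pain interference, mobility and upper extremity function (Introduction), and the Primary Outcome section describes it as covering quality of life as well as symptoms. PedsQL 3.0-RM covers pain and daily activities (Secondary Outcomes). A child who improves on drug treatment alone would tend to change on both.

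HRQOL improvement leads the hypothesis and is listed in the Discussion among the trial's intended implications. If the objective is reported as worded, an association could be offered as the answer to a question about effect.

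**Working it through.** **1. Question and method side by side**

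| Objective | Question | Method named in the objective | Arm contrast? |
|---|---|---|---|
| Primary | Effect of symptom management | C-Ped-PROMIS T-scores compared between arms | Yes |
| Secondary | How far symptom management improves HRQOL | Change in C-Ped-PROMIS related to change in HRQOL | No |

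The mismatch is in the text and needs no arithmetic. The remaining steps only illustrate its possible size.

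**2. Inputs**

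- Enrolment is 50 per arm, 100 in total, with about 20% loss (Sample Size Calculation). Completers: 100 × (1 − 0.20) = 80, or 40 per arm.
- Significance is two-sided at 0.05 (Statistical Analyses).
- Correlation r between the two changes: not given. Assumed |r| = 0.3, 0.5, 0.7, with 0 as a check.
- Treatment effect: set to zero on both scales.

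The plan's own sample size, for reference: (1.96 + 0.84)² × (10² + 10²) × 2 / (2 × 7²) = 7.84 × 400 / 98 = 32 per arm, and 32 / 0.8 = 40. The stated 50 per arm is not reproduced but lies above this figure. It concerns the primary outcome and has no bearing on this point.

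**3. Simulation under no treatment effect**

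Bivariate normal change scores, 4,000 trials per setting. Two tests were applied to each trial: a Pearson test of change against change over all children, and a between-arm t-test on HRQOL change. Entries are the percentage of trials with p < 0.05.

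| Assumed \|r\| | 80 children: correlation | 80 children: between-arm | 100 children: correlation | 100 children: between-arm |
|---|---|---|---|---|
| 0 | 4.7 | 5.3 | 4.8 | 5.3 |
| 0.3 | 78.8 | 5.4 | 86.6 | 4.7 |
| 0.5 | 99.8 | 5.0 | 99.9 | 5.7 |
| 0.7 | 100 | 5.0 | 100 | 4.3 |

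**4. Check by formula**

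With Fisher's transformation, power ≈ Φ(atanh(r) × √(n − 3) − 1.96). For n = 80, √77 = 8.775.

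- r = 0.3: 0.3095 × 8.775 − 1.96 = 0.76, so Φ ≈ 0.78.
- r = 0.5: 0.5493 × 8.775 − 1.96 = 2.86, so Φ ≈ 0.998.
- r = 0.7: 0.8673 × 8.775 − 1.96 = 5.65, so Φ ≈ 1.

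These agree with the simulation.

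**5. If the association is tested within one arm**

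For n = 40, √37 = 6.083, and the same formula gives:

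- r = 0.3: 1.883 − 1.96 = −0.08, about 47%.
- r = 0.5: 3.341 − 1.96 = 1.38, about 92%.
- r = 0.7: 5.276 − 1.96 = 3.32, above 99.9%.

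The figures are lower at r = 0.3, but in each case the result reflects the assumed correlation and not the treatment effect, which is zero throughout.

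**The case against.** The strongest objection is that a randomized comparison of HRQOL is already planned. Secondary Outcomes lists the HRQOL trajectory before the association, which enters only as an addition, and Statistical Analyses compares PRO trajectories between the two groups. The Introduction counts HRQOL among common PROs, so PedsQL can reasonably be read as covered. This stands, and it limits the consequence. A reader might infer that the trial has no between-arm HRQOL analysis, that its HRQOL conclusion must rest on a correlation, or that a real benefit would be missed. The article supports none of these. The planned analysis does not, however, correct the objective, which names a different method and makes no reference to it.

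A second objection is that the article states no correlation test and no rule by which a significant correlation would count as benefit, and that the association may be meant by arm. This also stands. The percentages illustrate how the named measure can behave; they do not describe a stated decision rule. An association reported by arm is still not an effect of the arm, because the same relationship in both arms is compatible with any difference in mean HRQOL, including none.

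A third objection is that the exact HRQOL contrast and time point can be left to a full protocol or SAP. That is accepted, and their absence is not part of this point. The point is that the article does state a method for the objective, and the method does not answer the question.

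It would also go too far to say that the same person completes both questionnaires at the same visit. The article sets reporters by age for C-Ped-PROMIS only, and follow-up forms are prompted by message or telephone. The overlap argument here rests on content alone.

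**Conclusion.** The point holds as a mismatch between the secondary objective and the method attached to it. The relationship between change in C-Ped-PROMIS and change in HRQOL is not a treatment effect and cannot show how far symptom management improves HRQOL. This conclusion follows from the text and does not depend on any assumed number.

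The size is illustrative. With 80 completers and no treatment effect, a test of the association would be significant in about 79% to 100% of trials for |r| from 0.3 to 0.7, against about 5% for a between-arm HRQOL test. This rests on normally distributed changes and on a correlation that the article does not give; at r = 0 the association test also stays at about 5%.

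Because a two-group comparison of PRO trajectories is already planned, this is a matter of stating the objective correctly and pointing it to that comparison. It should be corrected, since HRQOL leads the hypothesis.

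**What to change.** 1. **Objectives.** Replace the clause that begins with evaluating relationships by a between-arm comparison of the PedsQL 3.0-RM total score from baseline to 12 months, adjusted for the baseline score, reported with a 95% confidence interval, and made through the repeated-measures comparison already planned.
2. **Statistical Analyses.** Name the PedsQL 3.0-RM total score in the sentence on the two-group comparison of trajectories, so that objective and analysis agree.
3. **Secondary Outcomes.** Keep the change-change relationship as exploratory, reported by arm, and state that it is not evidence that the intervention improves HRQOL.

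The cost is wording in three places. No new data, patients or type of analysis are needed. The one thing given up is the standing of the association, which moves from the stated answer to an exploratory result.

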## Methods And Analyses

### Design and Setting

A longitudinal, randomized controlled trial will be carried out in outpatient and pediatric wards of the Shanghai Children's Medical Center (SCMC) affiliated to Shanghai Jiao Tong University School of Medicine between 1 September 2021 and 31 August 2023. The SCMC, a children' specialized hospital (level 3), is one of the main units of the National Children's Medical Center (NCMC). The number of patients with JIA in SCMC is approximately 1,500 per year. The implementation and reporting of this protocol will adhere to the standard protocol items: Recommendations for Interventional Trials (33) and the guidelines of Consolidated Standards of Reporting Trials (34). The trail is illustrated in a flowchart as shown in Figure 1.

**Figure 1 F1:**
[figure not shown]
Flow diagram of the trial.

### Participants

Participants are recruited from the outpatient and inpatient clinics. The main inclusion criteria for this trial are as follows: (1) meeting the diagnostic criteria for JIA of the Pediatric Rheumatology International Trials Organization (PRINTO); (2) aged 5 to 17 years; (3) the course of the disease is 3 months or more, and the family members have a certain degree of understanding of the disease; (4) patients and parents have normal understanding and expression skills and able and agree to respond to the questionnaire on the WeChat mini-program. Children diagnosed with early-onset ANA-positive JIA, other JIA, and unclassified JIA, or who combined with other major diseases that affect the quality of life, such as severe infections, are excluded.

### Consent

Following recruitment, a consent form is sent to the patient and family (parent/guardian) participants. The investigators explain the purpose and process of this study to the patient and family (parents/guardian), and they can put any questions to the investigators. Patients and their families are free to withdraw consent at any time during the study period (including the intervention period). Finally, they are required to sign the consent form.

### Sample Size Calculation

Sample size was calculated using the primary outcome –Pediatric Patient Reporting outcomes (Profile 25), and the “two mean comparison formula” as follows (35, 36): $n_{2}=\frac{{\left(z_{1-\alpha /2}+z_{1-\beta }\right)}^{2}(sd_{1}{}^{2}+sd_{2}{}^{2})(1+1/k)}{2{\left(mean_{1}-mean_{2}\right)}^{2}}$, *n*_1_ = *k*×*n*_2_, was used for the calculation. Z_1−**α**/2_ = 1.96, Z_1−**β**_= 0.84, according to the pre-experimental results, the mean ± standard deviation ($\overset{-}{\chi }$ ± SD) of ePRO group is 50 ± 10, and the ($\overset{-}{\chi }$ ± SD) of the control group is 43 ± 10. Taking into account the dropouts and lost follow-up rate of about 20%, we will finally enroll 50 participants in each group.

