### Randomization and Allocation

Following the signing of a consent form, participants are allocated in a 1:1 ratio to either ePROs-based group or control group based on the computer-generated random. Group numbers were sealed into the non-transparent envelopes kept by a specially appointed person. Because of the nature of interventions, the blinding of participants and investigators is impossible. But the data collectors who help to administer ePROs collection will be blinded to group allocation.

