### Outcomes and Measurement

#### Primary Outcome

The primary outcome of this study is the mean T-scores of patients in the ePROs-based group and the control group. The C-Ped-PROMIS is the primary ePRO tool, and it has eight short forms for assessing the child's symptoms and quality of life during the previous 7 days. Each form has a single dimension, and the 5-level Likert scoring method scale with the answers “never” (0) and “almost” always (4) is used for each item. Raw scores of each form are converted to standardized T-scores with a mean of 50 and a standard deviation of 10. Only all forms are answered completely and performed this conversion.

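### The printed sample size inputs give 40 enrolled per group after 20% loss, not the stated 50; the gap is conservative but unexplained

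*Protocol article*

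**What the plan says.** The Sample Size Calculation section of the protocol article bases the sample size on the primary outcome and prints a formula for comparing two means, with z values of 1.96 and 0.84. From pre-experimental results, the mean and SD "of ePRO group is 50 ± 10" and that "of the control group is 43 ± 10". The section does not report the number the formula yields. It goes straight to the conclusion: "Taking into account the dropouts and lost follow-up rate of about 20%, we will finally enroll 50 participants in each group".

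Three other places bear on the calculation:

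- Randomization and Allocation: "participants are allocated in a 1:1 ratio to either ePROs-based group or control group", so k = 1.
- Statistical Analyses: "A two-sided *p* < 0.05 is considered to be statistically significant", which agrees with z = 1.96.
- Abstract, Methods: one hundred children in total, which agrees with 50 per group.

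Power is never written as a percentage; z = 0.84 implies 80%.

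**The concern.** The section supplies the formula, every input, the loss allowance and the result, so a reader can repeat the calculation from start to finish. Doing so does not lead to 50. Because the evaluable number is left out, the reader cannot see at which step the figure departs from the inputs.

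What is at stake is whether the main planning figure can be reproduced. The enrolment may include a deliberate margin that is not described. Alternatively, one of the printed assumptions (difference, SD, power or loss rate) may not be the one that was used. The text does not let a reader tell which, and each would give a different account of what the trial was designed to detect.

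**Working it through.** **Inputs**

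- z for alpha 1.96 and z for power 0.84 (Sample Size Calculation)
- Means 50 and 43, so difference 7; SD 10 in each group (same section)
- k = 1 (Randomization and Allocation)
- Loss of about 20%; stated result 50 per group (Sample Size Calculation)

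**Step 1: the protocol's own formula**

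n = (z for alpha + z for power)² × (SD₁² + SD₂²) × (1 + 1/k) / (2 × difference²)

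n = (1.96 + 0.84)² × (100 + 100) × 2 / (2 × 49) = 7.84 × 400 / 98 = 3136 / 98 = 32.0 evaluable per group.

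**Step 2: the only adjustment named**

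32 / (1 − 0.20) = 40 enrolled per group, 80 in total. The cruder 32 × 1.2 = 38.4 gives 39. The stated figure is 50 per group, and 50/40 = 1.25, that is 25% more, or 20 children over both groups.

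**Step 3: can another standard reading of the same inputs give 50?**

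| Reading | Evaluable per group | Enrolled per group |
|---|---|---|
| Printed z values, n/0.8 | 32 | 40 |
| Unrounded z values, n/0.8 | 33 | 42 |
| t-test, n/0.8 | 33.02, so 34 | 42 to 43, depending on rounding |
| Printed or unrounded z values, n × 1.2 | 32 or 33 | 39 or 40 |
| One-sided test, n/0.8 | 26 | 33 |

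None does. Figures near 50 need an input that the section does not state:

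- 90% power gives 43 evaluable, hence 54 enrolled (n/0.8) or 52 (n × 1.2).
- The t-test size divided by an assumed worst-case Wilcoxon efficiency of 0.864 is 33.02/0.864 = 38.2 evaluable, hence about 48 enrolled. With an assumed efficiency of 0.955 the enrolled number is 33.02/0.955/0.8 = 43.2, so 44.
- A higher loss rate: 50 enrolled leaves 32 evaluable at 1 − 32/50 = 36% loss.

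**Step 4: what 50 per group delivers on the stated assumptions**

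This uses the normal approximation, as the protocol does. With 20% loss, 50 × 0.8 = 40 per group remain.

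- Power for 7 points: 7 / (10 × √(2/40)) − 1.96 = 3.13 − 1.96 = 1.17, which gives 87.9%.
- Difference detectable with 80% power: 2.80 × 10 × √(2/40) = 6.26, about 6.3 points.
- For comparison, power is 80.0% at 32 per group and 93.8% at 50 per group with no loss.

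A t-test at 40 per group gives 87.1%, so the choice of method does not alter the picture.

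**The case against.** The strongest reply is that 50 is a deliberate choice above a minimum. The formula fixes the smallest adequate number, the loss rate is only approximate, and the wording can be read as a decision taken after the calculation. The article also contains plausible motives for a margin. The Discussion voices strong concern about the response rate over a year, and the Statistical Analyses section plans Wilcoxon comparisons and an analysis by JIA subgroup. Enrolling above the minimum raises power and conflicts with nothing in the design.

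Much of this stands. Rounding up is possible, and the excess does no harm to power. What does not stand is that the article says so: none of these motives is linked to the 50, and the sentence attributes the figure to the 20% loss alone. Nor is this a detail lost in condensing the protocol, because the article prints both ends of the calculation and they do not meet.

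Two stronger readings are tempting and should be resisted:

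- A reader might infer that an input must have been misreported, or that 20 children are enrolled without reason. The documents cannot separate either from an unexplained margin.
- A reader might infer that the calculation belongs to a different outcome, because it is labelled "Pediatric Patient Reporting outcomes (Profile 25" while the Primary Outcome section says of the C-Ped-PROMIS that "it has eight short forms for assessing the child's symptoms and quality of life during the previous 7 days". The article never defines that label and itself calls it the primary outcome. The SD of 10 also matches the T-score scale. This shows an unexplained name and no more.

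**Conclusion.** The statement is wrong as written, and the point is minor. The printed inputs give 32 evaluable and 40 enrolled per group (80 in total), while the section attributes 50 per group (100 in total) to a loss rate of about 20%. Using unrounded z values or a t-test moves the derived enrolment only to 42 or 43.

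The direction is conservative. If the 7-point difference, the SD of 10 and the 20% loss hold, the trial has about 88% power where its inputs imply 80%. A reader might take the mismatch to mean that the trial is underpowered or that its power claim fails. The documents do not support that: no power percentage is written, and the number enrolled exceeds what the inputs require. The conclusion rests on 1:1 allocation, which is stated, and on reading z = 0.84 as 80% power.

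**What to change.** Keep 50 per group and restate the justification with one method throughout. By the protocol's own normal-approximation formula it could read:

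> 32 evaluable children per group give 80% power (two-sided 5% level) for a 7-point difference with SD 10; allowing for 20% loss requires 40 per group. We enrol 50 per group, which with 20% loss leaves 40 and gives about 88% power for 7 points, or 80% power for about 6.3 points.

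The sponsor should add its actual reason for the margin. If the 50 instead came from a different power, difference, SD or loss rate, correct that input. A loss rate of 36% should appear only if it was really the planning assumption.

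In the same edit, name the score to which 50 and 43 refer, in the terms used in the Primary Outcome section.

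The cost is about two sentences; enrolment and analysis do not change.
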